## Abstract

**Introduction:**

Research into what constitutes the best and most effective care for women with an acute severe postpartum mental disorder is lacking. The effectiveness and cost-effectiveness of psychiatric mother and baby units (MBUs) has not been investigated systematically and there has been no direct comparison of the outcomes of mothers and infants admitted to these units, compared with those accessing generic acute psychiatric wards or crisis resolution teams (CRTs). Our primary hypothesis is that women with an acute psychiatric disorder, in the first year after giving birth, admitted to MBUs are significantly less likely to be readmitted to acute care (an MBU, CRTs or generic acute ward) in the year following discharge than women admitted to generic acute wards or cared for by CRTs.

**Methods and analysis:**

Quasi-experimental study of women accessing different types of acute psychiatric services in the first year after childbirth. Analysis of the primary outcome will be compared across the three service types, at 1-year postdischarge. Cost-effectiveness will be compared across the three service types, at 1-month and 1-year postdischarge; explored in terms of quality-adjusted life years. Secondary outcomes include unmet needs, service satisfaction, maternal adjustment, quality of mother–infant interaction. Outcomes will be analysed using propensity scoring to account for systematic differences between MBU and non-MBU participants. Analyses will take place separately within strata, defined by the propensity score, and estimates pooled to produce an average treatment effect with weights to account for cohort attrition.

**Ethics and dissemination:**

The study has National Health Service (NHS) Ethics Approval and NHS Trust Research and Development approvals. The study has produced protocols on safeguarding maternal/child welfare. With input from our lived experience group, we have developed a dissemination strategy for academics/policy-makers/public.

Strengths and limitations of this studyWomen with lived experience of acute postnatal mental disorders have advocated a study of this kind for a number of years, and a lived experience group informed the development of this study.This study will be the first study to provide evidence on the relative effectiveness and cost-effectiveness of mother and baby units, generic acute psychiatric wards and crisis resolution teams.A randomised controlled trial study design was not possible due to the large geographical inequity in service provision leading to logistical challenges for randomisation, ethical difficulties in asking women for consent to randomisation when acutely distressed and ill, and strong service preferences of staff, women and families.

## Introduction

Severe postpartum psychiatric disorders are among the most challenging to treat as they are rapid in onset, can deteriorate quickly and are a leading cause of maternal death from suicide.^1^ These disorders may also be associated with deficits in caring for the newborn baby and disruptions in the mother–baby relationship.^1–3^ Over the longer term, the children of mothers admitted to inpatient psychiatric services may develop a range of health, developmental and mental health concerns.^4^ A recent examination of the costs of perinatal mental health problems indicates that the greatest costs relate to adverse child outcomes.^5^

Severe postpartum episodes (which include puerperal psychosis, severe depression or a relapse of bipolar disorder)^1 6^ require acute care which, in most countries, usually means hospital admission,^6^ either in psychiatric mother and baby units (MBUs; available in some parts of Europe, Asia, North America and Australia) or generic inpatient wards. MBUs admit mothers and babies together so that mothers can spend time with their baby as their mental state improves and, potentially, receive help for any difficulties in the mother–infant relationship.^7 8^ Such units are not, however, available everywhere internationally^9^ and data on effectiveness and cost-effectiveness are lacking. In the UK, MBUs are not equally distributed geographically, although this is gradually changing with recent new funding.^10^ The UK National Institute for Health and Care Excellence (NICE) and the Royal College of Psychiatrists recommend that women who develop severe postpartum disorders should be cared for in specialist psychiatric MBUs but evidence to inform commissioning of services on effectiveness and cost-effectiveness is lacking.

Historically, including at the time of recruitment to this study, women in the UK with acute postnatal illnesses could be admitted to generic acute wards, either because access to an MBU was not possible because of geographical distance or a lack of available beds; such admissions necessitate separation from the baby. Alternatively, women could be cared for at home by intensive home treatment teams, also known as crisis resolution teams (CRTs). CRTs care for people who do not require detention under the Mental Health Act but who are experiencing an acute psychiatric episode that would otherwise require hospitalisation. Such teams became available in all National Health Service (NHS) Trusts in England by 2005 and, depending on need, staff can visit service users in their homes daily to avoid acute admission.^11 12^ CRTs treat the mother in her own home and the baby can often remain with her and with her partner or other sources of support.

Research into what constitutes the best and most effective care for women with an acute severe postpartum mental disorder is lacking. The effectiveness and cost-effectiveness of MBUs has not been investigated systematically.^13^ Several studies of MBU admissions describe the clinical and parenting outcomes of mothers^14–20^; two studies report improvements in mother–infant interactions before and after participation in specific mother–infant video feedback interventions,^2 3^ although such before and after designs did not randomise mothers or use a control group comparison. Given limited resources and significant costs of specialist care services, there remains a pressing need for high-quality evidence of the clinical and cost-effectiveness of MBU admission for mothers and infants compared with generic acute wards or CRT services.^13^

Comparison of clinical interventions should be undertaken using a randomised controlled trial design. However, in this population, it is not considered ethical or practical to randomise women, in part because of the large distances many women would need to travel for admission to an MBU leading to logistical challenges for randomisation, ethical difficulties in asking women for consent to randomisation when acutely distressed and ill and because of strong preferences of staff, service users and families.^21^ Therefore, we have designed a quasi-experimental cohort study of women accessing different types of acute psychiatric services within the first year after birth, comparing women’s outcomes to determine clinical effectiveness and cost-effectiveness of MBUs with generic acute wards and CRTs.

## Objectives

Our primary objective is to test the hypothesis that women with an acute psychiatric disorder, in the first year after giving birth, who are admitted to MBUs are significantly less likely to be readmitted to acute care (MBU, CRT or generic acute ward) in the year following discharge from acute care compared with those admitted to generic acute wards or under the care of CRTs.

We also hypothesise that admission to MBUs will be cost-effective compared with admission to generic wards or CRTs for the period between index admission to 1-month postdischarge, and for the period from discharge from index admission to 1-year postdischarge.

We are also testing the following secondary hypotheses:

Women with an acute psychiatric disorder, in the first year after giving birth, admitted to an MBUWill have significantly fewer unmet health and social care needs 1-month postdischarge than those admitted to generic acute wards or under CRTs.Will report significantly higher levels of service satisfaction 1-month postdischarge than those admitted to generic acute wards or under CRTs.Will have better maternal adjustment 1-month postdischarge than those admitted to generic acute wards or under CRTs.Will be significantly more sensitive and less unresponsive when interacting with their babies 1-month postdischarge than those admitted to generic acute wards; similarly, their babies will be more cooperative and less passive.Will be more likely to retain custody of their child than those admitted to generic acute wards or under CRTs in the year following discharge from acute care.

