Modified Composite Abuse Scale	Self-report‡ 30-item questionnaire assessing experiences of partner abuse.^44^ Items are rated from 0=‘never’ to 5=‘daily’, with total scores ranging from 0 to 150. A cut-off point of 3 is assigned, with scores of 3 or more indicating partner violence. The scale has been modified for this study to collect data covering the two time periods: (1) prior to admission and (2) since discharge.	X	X		
Modified Social Provisions Scale	Researcher-administered‡ 24-item questionnaire that assesses the degree to which an individual’s social relationships provide various dimensions of social support.^45^ Items are rated on a four-point Likert scale ranging from 1=‘strongly disagree’ to 4=‘strongly agree’.^45^ 6 domains of social provision (ie, guidance, reassurance of worth, social integration, attachment, nurturance and reliable alliance) are calculated by summing the scores of specific items on the questionnaire; high scores on each of the domains indicate that the person is receiving that social provision. The scale has been modified to collect data covering the two time periods of interest for the study: (1) prior to admission and (2) since discharge.	X	X		
Short Form 36 Health Survey	Self-report‡ 36-item questionnaire which produces a preference-based single index measure of general health.^46^ It measures health on eight multi-item dimensions: (1) limitations in physical activities because of health problems; (2) limitations in social activities because of physical or emotional problems; (3) limitations in usual role activities because of physical health problems; (4) bodily pain; (5) general mental health (psychological distress and well-being); (6) limitations in usual role activities because of emotional problems; (7) vitality (energy and fatigue) and (8) general health perceptions.^47^ This measure can be used to calculate quality-adjusted life years (QALYs).		X		Primary
EuroQol five-dimension scale (EQ-5D-5L)	Self-report†‡ preference-based measure of health-related quality of life measured on five dimensions (mobility, self-care, usual activities, pain/discomfort and anxiety/depression), each rated on five levels (no problems, slight problems, moderate problems, severe problems and extreme problems).^48^ This measure can be used to calculate QALYs.		X	X	Primary

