### Power calculation

Our pilot data using the Clinical Record Interactive Search (CRIS) database (the anonymised Case Register^26^ local to King’s College Hospital, London) revealed the following for 20 perinatal women on generic acute wards, 20 admitted to MBUs and 20 under CRTs: acute ward patients were most likely to be readmitted to these services with 95% being readmitted at some point during 12-month follow-up, compared with 35% of women who received MBU care; CRT readmission rates were similar to MBUs. Therefore, assuming similar readmission rates nationally for MBU patients (35%), we could detect a doubling of risk for generic acute ward patients with 90% power with 47 women in each group. We aim to recruit 100 women in each group; to allow for 20% attrition and exclusion of women for being beyond the ‘region of support’ (ie, whose characteristics make them unmatchable with women in another treatment arm—see Statistical methods section for further details).

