## Analysis

### Statistical methods

There is limited availability of specialist MBU beds and it is, therefore, likely that some women who would be offered an MBU bed at first presentation are admitted to an acute ward, while waiting for a bed. As some women may also receive care from more than one type of inpatient service (ie, MBU and acute ward) during their index admission, in our main analysis MBUs will be classified as the ‘highest level of care’ and we will run two sensitivity analyses—one based the majority of days spent within a specific inpatient service and the other based on first service accessed.

We shall use a propensity score approach to account for systematic differences between MBU and non-MBU participants. This approach allows the exact specification of the covariate adjustment to be determined blind to the outcome data, thereby reducing the risk of unintended bias. The Stata command p score will estimate the propensity score of the treatment (MBU or non-MBU) on specified covariates, selected using problem knowledge and exploratory comparison of cohorts, using a probit model and will stratify individuals in blocks according to the propensity score. The blocks are determined by a balancing algorithm and the balancing property within each block is tested, to ensure sufficient blocks are used to adequately balance the covariates. We will also remove women with characteristics that place them beyond the ‘region of support’ and thus for whom there are no ‘matches’, that is, women with propensity scores either so high or so low that there are insufficient similar women receiving either MBU or non-MBU treatment to make a comparison; we will report characteristics and outcomes for these women separately.

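### The study is sized for MBU versus generic ward, but the analysis is built for pooled MBU versus non-MBU, which has less power and cannot support a claim against CRTs

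*Protocol article*

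**What the plan says.** Four places in the protocol article describe the comparison for the primary outcome, readmission to acute care within a year of discharge.

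- **Objectives.** MBU women are expected to be readmitted less "in the year following discharge from acute care compared with those admitted to generic acute wards or under the care of CRTs". The sentence can mean either comparator, both, or the two combined.
- **Abstract, Methods and analysis.** "Analysis of the primary outcome will be compared across the three service types, at 1-year postdischarge". The same paragraph adds: "Outcomes will be analysed using propensity scoring to account for systematic differences between MBU and non-MBU participants".
- **Power calculation.** "we could detect a doubling of risk for generic acute ward patients with 90% power with 47 women in each group". The MBU rate is taken as 35%. The pilot CRT rate is described as close to the MBU rate, and no power is given for a CRT or pooled contrast.
- **Statistical methods.** The Stata routine "will estimate the propensity score of the treatment (MBU or non-MBU) on specified covariates". The resulting weights go into the logistic regression for readmission, and average treatment effects are restricted to the common region of support.

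**The concern.** The sized contrast and the analysed contrast are different quantities. The first compares MBUs with wards. The second compares MBUs with a mixture of wards and CRTs. By the plan's own pilot description, half of that mixture (at the equal group targets) is readmitted at about the MBU rate, which dilutes the difference.

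Two things follow. The 90% power figure does not describe the test that the analysis section builds. And a pooled result driven entirely by wards could be reported under the Objectives wording as an advantage over CRTs. The introduction says evidence is needed to inform commissioning, so that misreading would matter.

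**Working it through.** **Inputs.** MBU 35%, and a doubling to 70% for wards (Power calculation). CRT taken as 35%, from the remark that pilot CRT and MBU rates were similar. Target 100 per group, and 100 × 0.80 = 80 after the stated 20% attrition. Region-of-support exclusions would lower this further. **Assumptions:** two-sided 5% (the article states no alpha), equal groups, no weighting or clustering.

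**1. The plan's own figure.** With p̄ = (0.35 + 0.70)/2 = 0.525:

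n = [1.960·√(2·0.525·0.475) + 1.282·√(0.35·0.65 + 0.70·0.30)]² / 0.35² = 40.7

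Continuity correction: (40.7/4)·[1 + √(1 + 4/(40.7·0.35))]² = 46.2, so 47 per group. The stated figure reproduces at two-sided 5%, for MBU versus ward.

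**2. Power of the pooled contrast.** The non-MBU rate is (0.70 + 0.35)/2 = 0.525, so the difference shrinks from 0.35 to 0.175. Power = Φ[(difference − 1.960·SE₀)/SE₁], where SE₀ uses the common rate and SE₁ the separate rates.

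- 80 MBU versus 160 non-MBU: SE₀ = 0.0683, SE₁ = 0.0664; Φ[(0.175 − 0.1339)/0.0664] = Φ(0.62) = 73%.
- 47 versus 94: SE₀ = 0.0891, SE₁ = 0.0866; Φ(0.004) = 50%.

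| Women per service group | MBU vs ward | Pooled MBU vs non-MBU |
|---|---|---|
| 47 | 93.8% | 50% |
| 80 | 99.6% | 73% |
| 100 | 99.9% | 82% |

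(No continuity correction in the table, which is why 47 per group gives 93.8% rather than 90%.)

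**3. Do the contrasts agree?** Simulated studies with rates 35/70/35% and 80 per group:

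- MBU vs ward significant: about 99.5%
- pooled significant: about 73%
- both wards and CRTs beaten: about 2%
- pooled significant while MBU vs CRT is not: about 71%

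**4. Error rate under no difference anywhere.** With equal groups, the ward z-statistic correlates 0.50 with the CRT one and 0.87 with the pooled one.

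| Rule | Two-sided | Favouring MBU only |
|---|---|---|
| One named contrast | 0.050 | 0.025 |
| Either pairwise contrast | 0.091 | 0.045 |
| Any of the three | 0.097 | 0.048 |
| Both pairwise contrasts | 0.009 | 0.005 |

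**5. Sensitivity.** At the pilot ward rate of 95%, the pooled non-MBU rate is (0.95 + 0.35)/2 = 65% and pooled power at 80 per group exceeds 99%. A pooled result without MBU vs CRT then occurs in about 95% to 97% of studies, depending on whether a CRT result against MBUs is counted. If the CRT rate were 40% to 55%, power for MBU vs CRT at 80 per group would be 10% to 72%.

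**The case against.** The strongest reply is that the methods point to one test. Treatment is defined as MBU or non-MBU, one set of propensity weights enters one regression, and the comparators in the Objectives can be read as a description of the non-MBU group. On that reading there is a single test and no multiplicity. Testing order and alpha allocation may also sit in an analysis plan that is not shown. Both points stand, and the absence of a hierarchy from the article is not itself a fault.

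They do not remove the conflict. The article never calls the pooled contrast primary, it sizes a different one, and its abstract announces a three-service comparison. If pooled is meant, the 90% power belongs to another contrast, and a pooled result still does not show an advantage over CRTs.

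It is also fair that 70% is a detectable rate rather than an expected one. At a 95% ward rate the power shortfall disappears, but the CRT problem grows.

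A reader might infer that the false-positive rate nearly doubles. The article does not support that as a general statement. It holds only if success on any one contrast counts, which no section says. Even then, the chance of a false claim in favour of MBUs is 0.045 to 0.048. A reader might also see extra primary endpoints in the labels that Table 1 gives to the economic measures. The Objectives place cost-effectiveness beside the primary objective and apart from the secondary list, and it is assessed by ratios and acceptability curves, so those labels add nothing to the error rate.

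**Conclusion.** The point holds as a mismatch between the sized contrast, the analysed contrast and the claim. At the rates used in the Power calculation, the pooled contrast has about 73% power at 80 per group (50% at 47), not 90%. In about 71% of studies it would be significant without a significant MBU versus CRT result.

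The power shortfall depends on a ward rate near 70%, and both figures depend on a CRT rate near 35%, which rests on 20 pilot women. Two-sided 5% is assumed, though it does reproduce 47. Weighting and region-of-support exclusions are ignored, so the power figures are probably optimistic. Family-wise error of about 0.09 is a conditional consequence. There is no inflation if one contrast decides or both must succeed.

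**What to change.** Before outcome analysis, state the following in the Objectives and Statistical methods:

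1. MBU versus generic ward, the sized contrast, decides at two-sided 5%.
2. MBU versus CRT is tested next at two-sided 5%, and is confirmatory only if the first is significant.
3. Each comparison uses weights and a region of support estimated for that pair of services, because a binary MBU/non-MBU score balances MBU women against wards and CRTs combined.
4. The pooled MBU versus non-MBU estimate is supportive.

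If the pooled contrast is kept as primary, restate the power for it, with the assumed CRT rate, and say that a pooled result alone does not support a claim against CRTs.

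The cost is some extra analysis work, since two pairwise scores and regions of support replace one, and there is no confirmatory CRT claim if the ward contrast fails. No further recruitment or data collection is needed, and the sized contrast keeps the full 5%.

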## Methods

Strengthening the Reporting of Observational Studies in Epidemiology reporting requirements for observational research have been followed (see online supplementary material).

10.1136/bmjopen-2018-025906.supp1Supplementary data

### Design

The study is a quasi-experimental cohort study embedded within existing service matrices.

### Service definitions

MBUs are defined here as units, with at least four beds and separate from other inpatient units, which provide specialised psychiatric care for both mother and baby where the mother has an acute perinatal psychiatric episode.^21 22^ Acute wards are defined as psychiatric wards that administratively record people receiving care as an inpatient admission, and which provide daily medical cover. CRTs are defined as intensive home treatment mental health teams that manage people in acute crises; the model of care includes rapid response, out of office hours multidisciplinary care.^23^ To ensure CRT treatment is available in study recruitment areas, CRTs have to be able to see people in mental health crises intensively (daily) where necessary; staff have to be available over an extended period (at least 12 hours a day) and the service has to have a specific crisis case load.

### Patient involvement

A lived experience group set up at the time of earlier pilot work (RP-DG-1108–10012) contributed to the writing of the grant proposal and the study design; the primary and secondary outcomes of importance to them; assisted in ensuring that data collection tools were accessible and comprehensible; these tools were then piloted in 21 women.

The lived experience group includes women (and their partners) recruited to represent the broadest possible spectrum of experience of perinatal mental health services. The group includes women who have experienced treatment in psychiatric wards, CRTs, community mental health services and MBUs. This group will continue to meet regularly throughout the duration of the study to advise on the execution and dissemination activities of the study.

### Study sample

Three cohorts of women with acute psychiatric disorders in the first year after childbirth, admitted to psychiatric MBUs, generic acute wards or CRTs are being recruited from mental healthcare provider organisations (Mental Health Trusts in England and Health Boards in Wales), selected to ensure diversity of urbanicity/rurality and access to MBUs. Women are eligible for the study if they used at least one acute service (MBUs, CRTs, generic acute wards), or any combination of all three, during the first year after childbirth.

